## Abstract

**Background:**

Pediatric obstructive sleep apnea/hypopnea syndrome (OSAHS) is a multifactorial syndrome caused by many risk factors, such as craniofacial anomalies, adenotonsillar hypertrophy, obesity, and airway inflammation. Although new treatment patterns have recently been proposed, treatment methods for children remain particularly challenging and controversial. This randomized controlled trial was designed to investigate the efficacy of adenotonsillectomy and/or orthodontic treatment for children who have mild OSAHS with mandibular retrognathia.

**Methods:**

A sample of 352 children with mild OSAHS and mandibular retrognathia, who are aged between 7 and 10 years, will be enrolled in the study. They will be randomized into four groups: the drug treatment group, the surgical treatment group, the orthodontic treatment group, or the surgery and postoperative orthodontic group. After randomization the children will receive treatments within 4 weeks. Outcome assessment will take place at the following points: (1) baseline, (2) 7 months after the treatment starting point, (3) 12 months after the treatment starting point, and (4) 24 months after the treatment starting point. The primary endpoint of the trial is the mean change in obstructive apnea/hypopnea index. Other endpoints will consist of the lowest oxygen saturation, apnea index, and hypopnea index assessed by polysomnography, subjective symptoms (assessed by the OSA-20 questionnaire), cephalometric measurements, and morphologic analysis of the upper airway.

**Discussion:**

The results of this study will provide valuable evidence for the merits and long-term efficacy of different treatment approaches and contribute to facilitating the multidisciplinary treatment of pediatric OSAHS.

**Trial registration:**

ClinicalTrials.gov: NCT03451318. Registered on 2 March 2018 (last update posted 19 April 2018).

## Administrative information

Note: the numbers in curly brackets in this protocol refer to SPIRIT checklist item numbers. The order of the items has been modified to group similar items (see http://www.equator-network.org/reporting-guidelines/spirit-2013-statement-defining-standard-protocol-items-for-clinical-trials/).

## Introduction

### Background and rationale {6a}

Obstructive sleep apnea/hypopnea syndrome (OSAHS) is a sleep disorder characterized by recurrent narrowing or collapse of the upper airway (UA), resulting in sleep fragmentation and multiple episodes of apnea and/or hypopnea [1]. Pediatric and adult OSAHS share a similar pathophysiology, i.e., a recurrent reduction or cessation of airflow caused by the narrow anatomic structure and defective function of the UA. However, they are actually different disease categories due to their different pathogeneses [2]. Adenotonsillar hypertrophy is currently the major cause of pediatric OSAHS, while in adults, the major risk factor may be obesity [3, 4].

The prevalence of pediatric OSAHS is reported to be between 2 and 10% in different countries [5]. Children with OSAHS may have a variety of problems, such as cardiovascular disorders, metabolic interferences, cognitive dysfunction, and attention problems [6–9].

Conventional treatments for OSAHS include adenotonsillectomy (AT), orthodontic treatment, continuous positive airway pressure (CPAP), medication, and weight loss [10]. At present, drug therapy is mainly applied in mild OSAHS or as a complementary method for other treatments [11, 12]. For severe OSAHS or obesity, medical management has clear limitations. CPAP, which expands the UA but does not regulate the underlying mechanisms of disease, was suggested as an effective treatment [13, 14]. CPAP has been used in OSAHS treatments for many years, but its clinical application is greatly limited by poor compliance [15]. It has been reported that 46–83% of adult patients cannot adhere to treatment when 4 h of nightly use is required [16]. For children, CPAP adherence varies between studies, but the application of CPAP at night is not optimistic due to their longer sleep hours. [17, 18]. Besides, additional data show that CPAP masks can have an adverse impact on the craniofacial development of a child, which means aggravating maxillofacial deformities and leading to increased collapsibility of the UA [19].

As the main reason for pediatric OSAHS is adenotonsillar hypertrophy, the primary treatment in children has always been AT, even though many studies have suggested that the efficacy of this treatment method may not be as favorable as expected [20]. Recent reports have confirmed that the efficacy of AT varies from 27.2 to 82.9% [21–23]. Recent evidence suggested that AT could ameliorate OASHS, but that the residual apnea/hypopnea index (AHI) may persist in some cases, especially in obese children [24, 25]. Orthodontic treatment has been widely used in recent years as an alternative or combination therapy with AT.

Craniofacial deformity has an obvious influence on the collapsibility of the UA [26, 27]. It can be a primary pathogenesis of OSAHS as well as a complication caused by long-term abnormal mouth breathing [28]. Mouth breathing is one of the main clinical symptoms of OSAHS in children, and it is common to find OSAHS among mouth breathers [29]. Mouth breathing during growth may alter the muscle tone of the oropharynx, which affects the development of maxillofacial structures and presents long faces, maxillary constriction, high arched palates, and mandibular retrognathia [28, 30]. The elimination of obstructive factors is the basis for nasal respiration and normal growth of maxillofacial bone and dentition [31]. Some cohort studies have observed that AT has the potential to block the progression of craniofacial malformation [32]. However, the roles of AT in dentofacial growth were found to be limited [15, 16, 33, 34] and could be achieved only if an AT was performed before 6 years of age [34, 35]. Dentofacial deformity was more unlikely to reverse spontaneously after AT surgery for children in the mixed dentition stage [36].

Therefore, clinical workers wondered whether it was necessary for all children with OSAHS to go to an orthodontist. Rapid maxillary expansion (RME) and mandibular advancement devices (MADs) are the most commonly used appliances for children with OSAHS [37–41]. RME benefits children with OSAHS through the following mechanisms: (1) it enlarges the dimension of the nasal cavity and increases nasal respiration; (2) it increases the maxillary width so that a better tongue position can be induced; (3) the normal width of the dental arch stimulates the development of the lower jaw. Camacho et al. stated in a systematic review that RME has stable long-term efficacy for pediatric OSAHS patients with transverse maxillary deficiency or narrow hard palates [39]. Villa et al. assessed the outcome of AT and RME in a non-randomized controlled trial and found that both of these treatment methods were effective, but further studies were needed to evaluate their long-term efficacy [42].

MADs, in the form of oral appliances, can promote the anterior displacement of the mandible and hyoid bone, leading to anterior traction of the tongue and thus an enlarged UA dimension. Pavoni et al. found that after MAD treatment, significant improvements in sagittal airway dimensions, hyoid position, and tongue position were induced, and obvious relief in subjective symptoms was observed in children with sleep-disordered breathing [43]. Many studies have reported that the clinical use of functional therapy for mandibular advancement such as twin-block and Frankel appliances significantly reduced AHI in patients with OSAHS [10, 40, 41]. In recent years, the combination of RME and MADs was illustrated by some clinicians.

For OSAHS children with adenotonsillar hypertrophy and dentoskeletal Class II malocclusions, who represent a large proportion of pediatric OSAHS patients, both orthodontic treatment and AT may be effective, but little evidence-based medical research has been found to our knowledge. There have been longstanding debates among clinicians about the indications for AT, especially for children with mild OSAHS. More convincing evidence is needed to prove that AT/orthodontic treatment has a therapeutic effect for children with OSAHS and that it improves the craniomaxillofacial deformity caused by mouth breathing.

### Objectives {7}

This clinical trial was designed to investigate the efficacy of AT and/or orthodontic treatment for OSAHS children with mild mandibular retrognathia. The efficacy will be evaluated by the improvement in subjective symptoms, polysomnography (PSG) data, UA structure, and maxillofacial development.

### Trial design {8}

This study will be a multicenter and randomized controlled pilot trial. Clinical research coordinators will explain the purpose and the procedure of this study to potential subjects. The participants will undergo a series of medical tests, which will include physical examinations, maxillofacial radiography, and polysomnography, to verify the diagnosis of OSAHS and malocclusion. Subjects will be randomly divided into one of four groups—the drug treatment group, the surgical treatment group, the orthodontic treatment group, or the surgery and postoperative orthodontic group—at a ratio of 1:1:1:1. Regardless of group assignment, tests will be conducted on each group before the treatment (M 0), 7 months after the treatment (M 7), 12 months after the treatment (M 12), and 24 months after the treatment (M 24). Figure 1 shows the flow chart of the research, and Table 1 shows the clinical trial schedule.

**Fig. 1 Fig1:**
[figure not shown]
Flow chart of study design

**Table 1 Tab1:** Schedule of enrollment, interventions, and outcome assessment

Action/timepoint	Enrollment	Baseline survey (M 0)	Randomization	Treatment	Follow-up (M 7)	Follow-up (M 12)	Follow-up (M 24)
Informed consent	⚪						
Demographic characteristics	⚪						
Medical history	⚪						
Physical examination	⚪						
Questionnaire (OSA-20)	⚪						
Lateral cephalometrics		⚪			⚪	⚪	⚪
Polysomnogram		⚪			⚪	⚪	⚪
Confirm suitability for study		⚪					
Allocation			⚪				
Drug treatment				⚪			
Surgical treatment				⚪			
Orthodontic treatment				⚪			
Surgery and postoperative orthodontic treatment				⚪			
Assessment							
Symptom changes					⚪	⚪	⚪
Questionnaire (OSA-20)		⚪			⚪	⚪	⚪
Cephalometric measurements		⚪			⚪	⚪	⚪
Morphologic analysis of UA		⚪			⚪	⚪	⚪
Polysomnogram		⚪			⚪	⚪	⚪
Safety assessment					⚪	⚪	⚪

## Methods: participants, interventions, and outcomes

### Study setting {9}

Participants will be recruited at Shanghai Stomatological Hospital, Shanghai Ninth People’s Hospital affiliated to Shanghai Jiao Tong University, and Shanghai Children’s Hospital, all of which are located in Shanghai, China, from May 2018 to December 2021 (anticipated). These hospitals in Shanghai comprise relevant diagnostic and treatment departments required for this study, including ear, nose, and throat and stomatological departments. Notification of subject recruitment will be published in these three hospitals and on their official websites.

### Eligibility criteria {10}

All participants will be assessed by a treatment group consisting of more than three experienced pediatric physicians, otolaryngologists, and orthodontists.

#### Inclusion criteria

The inclusion criteria for the study are as follows:
Patients aged 7–10 yearsPatients diagnosed with mild OSAHS (an apnea index of 1–5 events per hour according to PSG)Patients with hypertrophy of the tonsils or adenoidsPatients with mouth breathingPatients with constricted dental arch or mandibular retraction (A point, nasion, B point [ANB] ≥ 4.5)Patients whose guardians agree to enter this trial and sign the relevant informed consent form.

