## Interventions

### Explanation for the choice of comparators {6b}

Due to poor compliance, the application of CPAP for pediatric OSAHS is decreasing in the clinic. The most commonly used treatments are medication, AT, and orthodontic treatment. For children with mild OSAHS and mandibular retrognathia, both orthodontic treatment and AT may be effective in terms of PSG data and maxillofacial development, but there is no evidence-based medical research to compare the efficacy of AT and/or orthodontic treatment. Furthermore, we wondered what the indications are for the use of these two therapies, individually or in combination. Thus, in this study, the comparators included a drug treatment group, a surgical treatment group, an orthodontic treatment group, and a surgery and postoperative orthodontic group.

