#### Cephalometric measurements

Lateral cephalometric radiographs will be taken for all the subjects at the intercuspal occlusion and then traced and digitized using the software Dolphin Imaging (Dolphin Imaging & Management Solutions Corporation, Chatsworth, CA, USA). The cephalometric measurements are presented in Fig. 3. The measurement items are as follows: SNA, angular indicator for assessment of maxillary protrusion; SNB, angular indicator for assessment of mandibular protrusion; ANB, angular indicator for assessment of the sagittal relationship between the jaws; MP-FH, angle between the mandibular plane and Frankfort plane; MP-SN, angle between the mandibular plane and SN plane; UI-SN, angular indicator for assessment of upper anterior teeth protrusion; LI-MP, angular indicator for assessment of lower anterior teeth protrusion; UL-Ep, distance between upper lip and the aesthetic plane; LL-Ep, distance between lower lip and the aesthetic plane.

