## Discussion

Cranial and maxillofacial growth and development in children are influenced by both genetic and environmental factors [46]. The change of respiratory mode in children may alter the oropharyngeal muscle tone, which affects the development of maxillofacial sections. Mouth breathing is one of the main clinical symptoms of OSAHS in children, and it is common to find facial features such as long faces, maxillary constriction, high arched palates, and mandibular retrognathia among mouth breathers [28, 30]. The contraction of the upper airway (UA) is closely related to this kind of maxillofacial deformity, while maxillofacial deformities can also be the primary or promoting factor for OSAHS. The longer mouth breathing continues and the more serious the skeletal alterations that occur in OSAHS children, the more difficult it will be to cure the OSAHS. Therefore, early diagnosis of the morphologic analysis of the UA and maxillofacial structure is crucial for pediatric OSAHS. In this study protocol, CBCT of subjects will be performed for both morphologic analysis of the UA and cephalometric measurements to assist in diagnosis and efficacy evaluation. Traditional and commonly used efficacy evaluation methods in pediatric OSAHS such as PSG and the OSA-20 questionnaire are also included in this study.

Although new treatment patterns have recently been proposed, treatment methods for children have continued to be particularly challenging [26]. Furthermore, there is still great controversy concerning the treatment of OSAHS in clinic due to the lack of randomized controlled studies comparing treatment approaches. In this study, a multicenter randomized controlled trial was designed to investigate the advantages and disadvantages of AT and/or orthodontic treatment for children with mild OSAHS and mandibular retrognathia.

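### The entry criterion admits children without mandibular retrognathia, while the abstract, objective and Discussion state the population as children who have it

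*Protocol article*

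**What the plan says.** The protocol article gives two versions of who is in the trial.

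- **Entry rule** (Eligibility criteria {10}, Inclusion criteria): besides age, mild OSAHS, enlarged tonsils or adenoids, mouth breathing and consent, the child must have "constricted dental arch or mandibular retraction (A point, nasion, B point [ANB" of at least 4.5). The exclusion criteria cover central apnoea, systemic disease, rhinostenosis and extreme BMI. None concerns jaw relation.
- **Stated population**: the abstract's Background speaks of "orthodontic treatment for children who have mild OSAHS with mandibular retrognathia", and its Methods of "A sample of 352 children with mild OSAHS and mandibular retrognathia". The comparator section {6b} argues that "For children with mild OSAHS and mandibular retrognathia, both orthodontic treatment and AT may be effective". The Discussion says that the trial weighs "AT and/or orthodontic treatment for children with mild OSAHS and mandibular retrognathia", and its limitations paragraph names the selection of such children as the first challenge.
- **Objective** {7}: here the population is "OSAHS children with mild mandibular retrognathia", so the adjective has moved from the sleep disorder to the jaw finding.

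ANB is measured in every child. The cephalometric section lists "ANB, angular indicator for assessment of the sagittal relationship between the jaws", and Table 1 schedules lateral cephalometry at the baseline survey, before randomisation.

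**The concern.** A trial's conclusion applies to the children its entry rule lets in. Here that rule is wider than the population named almost everywhere else. If the report keeps the article's label, readers will take the result as evidence about children with mild OSAHS and mandibular retrognathia, when an unknown fraction may have had a narrow arch and an ANB below the cut-off.

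This is not detail left to a fuller protocol or an analysis plan: the article states both versions and they differ. As described, the report would not reveal the size of the gap. Baseline ANB is neither a minimisation factor (Implementation {16c}: sex and obesity) nor a covariate in the primary ANCOVA (Statistical methods {20a}: gender, obesity status, baseline AHI), and the article plans no breakdown by it.

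**Working it through.** **1. Does the rule require retrognathia?** Take a child who meets every other criterion, has a constricted arch and has an ANB below 4.5. The arch-or-retraction item is met by its first half, and no exclusion applies. The child is eligible.

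**2. Does another step close the gap?**
- Eligibility criteria {10} has specialists, including orthodontists, assess every participant, but adds no criterion.
- Trial design {8} says that tests verify OSAHS and malocclusion. It does not say that the malocclusion must be mandibular retraction.
- Table 1 has a step confirming suitability, judged against the same criteria.

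None of these adds a retrognathia requirement.

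**3. Could the ANB cut-off govern both halves of the item?** That reading is strained. The cut-off follows the words on retraction, and the article defines ANB as a sagittal indicator, whereas arch constriction is transverse. If it was intended, the sentence still has to be rewritten.

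**4. The stated sample size.** 80 per group × 4 = 320, and 320 × 1.10 = 352, which reproduces the article's total. The abstract applies the retrognathia label to all 352.

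**5. How many children could be mislabelled?** Let q be the share admitted with ANB below 4.5. The article gives no value, so the values below are assumptions. The number affected is 352 × q:
- q = 0.10: 35.2
- q = 0.20: 70.4
- q = 0.40: 140.8

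**6. What could an analysis of the children meeting the cut-off still show?** With 80 evaluable per arm, 80 × (1 − q) per arm meet it. For one pairwise contrast at a standardised difference of 0.4 (reading the article's effect value of 0.4 this way), normal-approximation power is Φ(0.4 × √(n/2) − z), with z = 1.960 two-sided or 1.645 one-sided at 5%:

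| q (assumed) | n per arm | two-sided | one-sided |
|---|---|---|---|
| 0 | 80 | 0.716 | 0.812 |
| 0.10 | 72 | 0.670 | 0.775 |
| 0.20 | 64 | 0.619 | 0.732 |
| 0.40 | 48 | 0.500 | 0.624 |

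The article does not state sidedness, so both columns are shown. An analysis by ANB can be supportive, but should not carry the main conclusion.

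**7. The word *mild*.** The inclusion criteria, abstract, comparator section and Discussion attach it to OSAHS. Only the objective attaches it to retrognathia.

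**The case against.** The best defence is that this is only a label. Eligibility is fixed before randomisation, so children admitted on arch constriction alone are spread over all four arms in expectation and bias no contrast. The closing statement of the Discussion also claims a contribution to paediatric OSAHS generally. The first part stands and limits the point to whom the result describes. The second does not remove the mismatch, because the abstract, comparator section and Discussion still name the narrower group.

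A reader might infer more than the article supports:

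- **That the treatment effect is diluted by q.** This needs a value for q and an assumption that mandibular advancement does nothing without retrognathia. The Background {6a} makes no such condition: it explains the benefit by forward movement of the mandible and hyoid and a larger airway, and cites children with sleep-disordered breathing. No arm isolates that component.
- **That half of these children receive an unsuitable appliance, which is a safety matter.** Two of four equal arms do use the twin-block, but combined with RME, which the Background justifies for narrow arches. No passage supports a safety claim.
- **That ANB is the wrong measure because SNB describes the mandible.** The article fixes a reproducible cut-off, and SNB is already among the measurements planned at baseline.
- **That the main conclusion should rest on the retrognathic subset.** This would lose power, as the table shows.

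The misplaced *mild* is a slip whose meaning is recoverable from the other sections. It adds little weight but should be corrected.

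**Conclusion.** The point holds as a contradiction between the entry criterion and the stated population. As written, the trial cannot claim that all 352 children have mandibular retrognathia, and a conclusion worded for that group would cover an unknown share who may not. The share could be small: many children with a constricted arch may also meet the ANB cut-off, and the article gives no data either way. The counts above only illustrate assumed values of q, and the contradiction does not depend on them. The consequence is for labelling and generalisability. The article gives no ground for inferring a biased or invalid randomised comparison, a quantified loss of effect or harm to participants.

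**What to change.** Reconcile the inclusion criterion with the population statements. Which criterion was intended is for the sponsor to say.

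If the *or* stands:

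1. State the population in the abstract, objective and conclusion as mild OSAHS with constricted dental arch and/or mandibular retrognathia.
2. Keep all randomised children in the primary analysis, excluding none because of baseline ANB. The choice between the ITT and PP sets is a separate matter.
3. Report, by arm, the number with ANB of at least 4.5 at baseline.
4. Add a supportive analysis of the change in AHI from M 0 to M 7 by that pre-randomisation variable, labelled as supportive and specified before the data are analysed.

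If retrognathia was meant to be required of every child, the criterion has to say so. Items 3 and 4 are then still needed for children already enrolled under the present wording. Recruitment has run since May 2018, and the Discussion already expects difficulty in finding eligible children, so this route costs recruitment.

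In either case, correct the objective so that *mild* qualifies OSAHS.

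Keeping the *or* costs a text amendment, one extra baseline row and one extra analysis, with no new data collection. The price is a somewhat broader claim and a subgroup analysis with lower power than the main comparison.
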